|                                                                    | Cervical mucus (PK LNG)                                           |                                                   |                          |                                  |         |                                         |                                  |                                | ✓        | ✓                           | ✓                              |                                             |                                 |  |
|                                                                    | Cervical mucus (PD LNG)                                           |                                                   |                          |                                  |         |                                         |                                  |                                | ✓        |                             |                                |                                             |                                 |  |
|                                                                    |                                                                   |                                                   |                          |                                  |         |                                         |                                  |                                |                      |                             |                                |                                             |                                 |  |
|                                                                    | Transvaginal Ultrasound (PD LNG)                                  |                                                   |                          |                                  | ✓       |                                         |                                  |                                |                      |                             | ✓                              |                                             |                                 |  |
|                                                                    | Endometrial biopsy (Expl PD LNG, safety)  (EVMS only) |                                                   |                          |                                  | ✓       |                                         |                                  |                                |                      |                             | ✓                              |                                             |                                 |  |
|                                                                    | Cerv/vag biopsies:                                                | Expl PD TFV (1, EVMS only)                        |                          |                                  |         | ✓                                       |                                  |                                |                      |                             | ✓                              |                                             |                                 |  |
|                                                                    |                                                                   | Safety (2 EVMS/1 DR)                              |                          |                                  |         | ✓                                       |                                  |                                |                      |                             | ✓                              |                                             |                                 |  |
|                                                                    |                                                                   | PK TFV, TFV-DP (both clinical sites)  |                          |                                  |         |                                         |                                  |                                | ✓ (2)                |                             | ✓ (2)                          | ✓ (1)                           | ✓ (1)               |  |
| Acceptability questionnaire                                        |                                                                   |                                                   |                          |                                  |         |                                         |                                  |                                |                      | ✓                           |                                |                                             |                                 |  |
| Review guidebook, record AEs, CTs, menses, etc.                    |                                                                   |                                                   |                          |                                  |         | ✓                                       | ✓                                | ✓                              | ✓        | ✓                           | ✓                              | ✓                                           |                                 |  |
| Confirm followed instructions re: intercourse and vaginal activity |                                                                   |                                                   |                          | ✓                                | ✓       | ✓                                       | ✓                                | ✓                              | ✓                    | ✓                           | ✓                              | ✓                                           |                                 |  |

|                                                          | Screening/
Enrollment | Pre-treatment Cycle  |         | IVR in place                            |                |                                |                      |                             | After IVR removal              |                                             |                                 |
|----------------------------------------------------------|--------------------------|----------------------------------|---------|-----------------------------------------|----------------|--------------------------------|----------------------|-----------------------------|--------------------------------|---------------------------------------------|---------------------------------|
| Visit #                                                  | Visit 1                  | Visit 2                          | Visit 3 | Visit 4 
(IVR insertion) |                | Visit 5
(24 h p
Visit 4) | Visit 6  | Visit 7
(IVR
removal) | Visit 8
(24 h p
Visit 7) | Visit 9 
(72 h p
Visit 7) | Follow-
up call /
contact |
|                                                          |                          |                                  |         | Pre-
insertion                       | Post-insertion |                                |                      |                             |                                |                                             |                                 |
| Dispense or collect guidebook                            |                          |                                  | ✓       |                                         |                |                                |                      |                             | (✓)                            | ✓                                           |                                 |
| Dispense ovulation predictor kit                         |                          |                                  |         |                                         |                | ✓                 |                      |                             |                                |                                             |                                 |
| Collect IVR, complete IVR processing (photography, etc.) |                          |                                  |         |                                         |                |                                |                      | ✓                           |                                |                                             |                                 |
| Study exit                                               |                          |                                  |         |                                         |                |                                |                      |                             |                                |                                             | ✓                               |

 P4 will be drawn on Day 21 (Visit 2). If the result is  $\geq 3$  ng/ml, the participant will return for Visit 3. If P4  $<3$  ng/ml at Visit 2, repeat testing will be done on Day 23 (repeat Visit 2). If the repeat testing yields a serum P4 of  $\geq 3$  ng/mL, the participant will return for Visit 3. If the P4 at repeat Visit 2 is  $<3$  ng/mL, the participant will be discontinued.

 IVR insertion will be on Day 7 of the menstrual cycle. Initial IVR insertion at Visit 4 will be witnessed by clinic staff.

 Some procedures from Visit 6 will be repeated if the participant has a positive ovulation predictor kit test following Visit 6. At repeat Visit 6, AEs, CTs and menses information will be reviewed, blood will be drawn to assess LNG PD (estradiol) and cervical mucus will be collected for LNG PK/PD.

 Visit 9 will only occur for those randomized to this collection time point for PK biopsy.

 Participants will be randomized to one of the following time points for pelvic exam and genital specimen collection: 1, 2, 4, or 8 hours after IVR insertion

 At Visit 5 and Visit 7 (pre-removal), 3 swabs for TFV PK will be collected: near the IVR, about 2/3 of the distance from the posterior fornix to the introitus, and on the ectocervix, in an effort to demonstrate correlation between the less invasive assay (swab) and more invasive assay (biopsy). At Visit 4 (post-insertion), Visit 6 and Visit 8, 1 swab will be collected from near the IVR to assess correlation between swabs and aspirates.

 EVMS only. Endometrial biopsies will be split with one specimen being assayed for morphometric analysis and endometrial dating and the other being analyzed for markers of progestational effects.

 One or two biopsies will be taken, as indicated by the number in parentheses. If only one is taken, it will be located near the IVR position. If two are taken, one will be near the IVR position and the other about 2/3 of the distance from the posterior fornix to the introitus.

 Participants will be randomized to one of the following time points for one proximal biopsy: Visit 8 (24 hours post IVR removal) or Visit 9 (72 hours post IVR removal).

 Participants will start using the ovulation predictor kit on Day 10 of their cycle and will notify the clinic on the day it becomes positive. They will be seen that day or as soon as possible afterward, and will continue testing until the morning of Visit 6. If it does not turn positive by Day 16, they will come in for Visit 6 no later than Day 17 and will continue use of the predictor kit following Visit 6.

**Table 4: Relationship of Study Visits to IVR Day and Cycle Day**

|           | Screening/
Enrollment | Pre-treatment Cycle |         | IVR in place         |         |                      |                      | After IVR removal |         |
|-----------|--------------------------|---------------------|---------|----------------------|---------|----------------------|----------------------|-------------------|---------|
| Visit #   | Visit 1                  | Visit 2             | Visit 3 | Visit 4  | Visit 5 | Visit 6  | Visit 7  | Visit 8           | Visit 9 |
| IVR Day   |                          | ~ -14               | ~ -10   | 1                    | 2       | ~8                   | ~16-18               | ~17-19            | ~19-21  |
| Cycle Day | Any day                  | 21                  | 24      | 7                    | 8       | ~14                  | ~22-24               | ~23-25            | ~25-27  |

 IVR insertion

 Visit 6 to occur as close as possible to day of ovulation, but no later than Day 17. Some procedures from Visit 6 may be repeated if ovulation occurs after Day 17.

 IVR removal. Visit 7 should occur 8-10 days after Visit 6 or repeat Visit 6

## 7.2. Anticipated Length of Study

Recruitment for the study is expected to take approximately 6 to 8 months. Each participant is expected to complete the study in about 3 months. Therefore, the clinical portion of the study is expected to be completed in about 9 to 11 months. Lab assays are expected to take an additional 3 to 4 months. Data analysis is expected to take approximately 3 months and preparation of the final report 2 additional months.

## 7.3. Number of Subjects

Approximately 100 women may be consented and undergo assessment procedures in order to have at least 50 women complete the study.

## 7.4. Treatment Assignment

Five treatment codes (A1-E5) will be randomly assigned to treatment group such that 2 codes are randomly associated with each of the two active groups (TFV/LNG and TFV-only) and 1 code is associated with the placebo ring. Participants will be randomized to one of the 5 codes, stratified by center, in a 1:1:1:1:1 ratio. This will effectively randomize women to treatment group in a 2:2:1 ratio (TFV/LNG:TFV-only:placebo).

## 7.5. Criteria for Study Termination

Recruitment for the study or a treatment arm may be stopped at one or both sites if, in the opinion of CONRAD:

- Review of AEs shows an unexpected, significant or unacceptable risk to the participants enrolled in the study or treatment arm (AEs will be monitored by the Clinical Study Leader and a decision to discontinue the study because of safety will take into account whether the AEs were possibly product-related, were serious, and/or led to participant discontinuation)
- The site has failed to enroll subjects at an acceptable rate
- The protocol requirements have not been adhered to and/or
- Administrative reasons

## 8. SELECTION AND WITHDRAWAL OF PARTICIPANTS

The volunteers for this study will be recruited using a variety of methods, including through existing databases (as protected health information permits) and through advertisements in local media outlets which have been approved by the local Institutional Review Board (IRB).

Women will be recruited since vaginal rings can only be used by women and the endpoints require genital sampling. Although the National Institutes of Health (NIH) has mandated that children, defined as younger than 21 years old, be included in research trials when appropriate, this study fits one of the “Justifications for Exclusion” as set forth by the NIH. Specifically, “insufficient data are available in adults to judge potential risk in children” and “children should not be the initial group to be involved in research studies.” We will recruit children aged 18 to 20 years who can legally provide informed consent. Efforts will be made by the sites to recruit subjects so that the racial and ethnic characteristics of the subject population will reflect the demographics of the study sites. No selection criteria shall be based on race or ethnicity.

### 8.1. Inclusion Criteria

Volunteers must meet all of the following criteria prior to genital sampling at Visit 3.

- Age 18-45 years, inclusive
- General good health (by volunteer history and per investigator discretion) without any clinically significant systemic disease (including, but not limited to significant liver disease/hepatitis, gastrointestinal disease, kidney disease, thyroid disease, osteoporosis or bone disease, and diabetes)
- Currently having regular menstrual cycles of 26-35 days by participant report
- History of Pap smears and follow-up consistent with standard medical practice as outlined in the study manual or willing to undergo a Pap smear
- Protected from pregnancy by one of the following:
  - Sterilization of either partner. *Note: Women protected from pregnancy by sterilization of either partner must abstain from vaginal intercourse from 48 hours prior to Visit 3 until the sixth day after the last study visit.*
  - Willing to abstain from vaginal intercourse from Visit 1 until the sixth day after the last study visit.
- Willing to abstain from any other vaginal activity and the use of vaginal product other than the study product including tampons, spermicides, lubricants, and douches starting 48 hours before Visit 3 until the sixth day after the last study visit
- Vaginal and cervical anatomy that, in the opinion of the investigator, lends itself to easy colposcopy and genital tract sample collection
- Negative urine pregnancy test
- $P4 \geq 3$  ng/ml

- Willing to give voluntary consent, sign an informed consent form and comply with study procedures as required by the protocol

## 8.2. Exclusion Criteria

Volunteers must meet none of the following criteria prior to genital sampling at Visit 3.

- BMI  $\geq 30$  kg/m^2
- History of hysterectomy
- Currently pregnant or within two calendar months from the last pregnancy outcome. *Note: If recently pregnant must have had at least two spontaneous menses since pregnancy outcome.*
- Use of any hormonal contraceptive method in the last 3 months (oral, transdermal, transvaginal, implant, or hormonal intrauterine contraceptive device)
- Injection of Depo-Provera in the last 10 months
- Use of copper IUD after Visit 1
- Currently breastfeeding or having breastfed an infant in the last two months, or planning to breastfeed during the course of the study
- History of sensitivity/allergy to any component of:
  - TFV 1% gel
  - Topical anesthetic, or allergy to both silver nitrate and Monsel's solution
- Contraindication to LNG
- In the last six months, diagnosed with or treated for any STI or pelvic inflammatory disease. *Note: Women with a history of genital herpes or condylomata who have been asymptomatic for at least six months may be considered for eligibility.*
- Nugent score greater than or equal to 7 or symptomatic bacterial vaginosis (BV) as defined by Amsel's criteria
- Positive test for *Trichomonas vaginalis*, *Neisseria gonorrhea* (GC), *Chlamydia trachomatis* (CT), HIV, or Hepatitis B surface antigen (HBsAg)
- Known bleeding disorder that could lead to prolonged or continuous bleeding with biopsy
- Chronic or acute vulvar or vaginal symptoms (pain, irritation, spotting, etc.)
- Known current drug or alcohol abuse which could impact study compliance
- Grade 2 or higher laboratory abnormality, per the August 2009 update of the Division of AIDS, National Institute of Allergy and Infectious Disease (DAIDS) Table for Grading the Severity of Adverse Events, or clinically significant laboratory abnormality as determined by the clinician
- Systemic use in the last two weeks or anticipated use during the study of any of the following: corticosteroids, antibiotics, anticoagulants or other drugs known to prolong bleeding and/or clotting, antifungals, CYP3A4 inducers or inhibitors (e.g., St. John's Wort or erythromycin), antivirals (e.g., acyclovir or valacyclovir) or antiretrovirals (e.g., Viread, Atripla®, Emtriva®,

Complera®). *Note: Participants should avoid non-steroidal anti-inflammatory drugs (NSAIDs) except for treatment of dysmenorrhea during menses. Participants may use Tylenol® on an as-needed but not daily basis during the study.*

- Participation in any other investigational trial (device, drug, or vaginal trial) within the last 30 days or planned participation in any other investigational trial during the study
- History of gynecological procedures (including genital piercing) on the external genitalia, vagina or cervix within the last 14 days
- Abnormal finding on laboratory or physical examination or a social or medical condition which, in the opinion of the investigator, would make participation in the study unsafe or would complicate interpretation of data

## **8.3. Participant Withdrawal**

### **8.3.1. Withdrawal Criteria**

Participants who sign the informed consent and agree to participate in the study but do not meet eligibility criteria will not undergo initial genital sampling procedures (Visit 3) and will not continue in the study. No case report forms (CRFs) will be completed for participants who do not undergo initial genital sampling.

Once a participant undergoes initial genital sampling procedures, she may be withdrawn from the study for the following reasons:

- Failure to follow protocol requirements that is judged severe enough by the investigator to significantly affect study outcomes
- Pregnancy or desire to become pregnant
- Use of exogenous hormones including systemic corticosteroid therapy
- Medical reasons, including diagnosis of an STI or symptomatic BV
- Personal reasons (participant request)
- Discontinuation of treatment arm, her site, or of entire study (Section 7.5)

### **8.3.2. Replacement**

At least fifty women will complete the study. Participants who are randomized but do not complete all genital sampling will contribute to the analysis as described in Section 14 but additional volunteers may be enrolled until the target number of completers is achieved. Participants who initiate ring use but discontinue prior to completion may not re-enroll.

---

 Drugs such as Tylenol that can affect liver function and drugs that affect renal function may affect metabolism and should not be used on a daily basis during the study.

### **8.3.3. Follow-up**

If the participant discontinues from the study after Visit 3 but prior to completing all genital sampling, the site may ask her to return for study procedures, if she is willing and if appropriate. She will be asked about medications taken and AEs including genital symptoms since the last visit. If she undergoes biopsy procedures, she will be contacted by telephone approximately one to two weeks after the biopsy. She will be exited from the study during her last contact with the site.

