## 9.10. Follow-up Call/Contact

The site will contact the participant about one to two weeks after the completion of study visits. She will be asked about AEs experienced and medications taken since the last visit. The participant will then be exited from the study, unless she has symptoms that require follow-up.

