## **13. ADVERSE AND SERIOUS ADVERSE EVENTS**

### **13.1. Definition of Adverse Events (AE)**

An AE is any untoward medical occurrence associated with the use of an investigational product in humans, whether or not considered product related. An AE can therefore be any unfavorable and unintended sign (including an abnormal laboratory finding), symptom, or disease temporally associated with the use of an investigational product, whether or not considered related to the investigational product. Pre-existing events that increase in frequency or severity in nature during or as a consequence of use of an investigational product in human clinical trials will also be considered as AEs. Any medical condition or clinically significant laboratory abnormality with an onset date before the first date of study product administration is considered to be pre-existing, and should be documented in the source document for the participant.

All AEs starting with Visit 3 before treatment, during treatment, or by the time of the follow-up call one to two weeks after the last study visit, whether or not they are related to the study, must be recorded on forms provided by CONRAD.

According to 21 CFR 312.32 “IND Safety Reports” the following definitions of terms apply to AEs occurring in clinical studies involving drugs.

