#### **13.1.3. Serious Adverse Event (SAE) or Serious Suspected Adverse Reaction**

An AE or suspected adverse reaction is considered “serious” if, in the view of either the investigator or the sponsor, it:

- Results in death;

- Is immediately life-threatening;
- Requires in-patient hospitalization or prolongation of existing hospitalization;
- Results in persistent or significant disability or incapacity;
- Results in a congenital abnormality or birth defect; or
- Is an important medical event that may jeopardize the patient or may require medical or surgical intervention to prevent one of the outcomes listed above.

All SAEs starting with Visit 3, before treatment, during treatment, or by the time of the follow-up call/contact one to two weeks after the last study visit, whether or not they are related to the study, must be recorded on forms provided by CONRAD.

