### **13.4. Reporting Serious Adverse Events**

All SAEs whether or not considered a suspected drug reaction will be recorded starting with Visit 3, before treatment, during treatment, or by the time of the follow-up call/contact one to two weeks after the last study visit.

Any SAE including those listed in the protocol or investigator brochure must be reported to CONRAD within 24 hours of discovery. If there is any question whether the event meets the criteria for “serious” it should be reported anyway. In addition, a completed SAE Form must be faxed or emailed to CONRAD as soon as possible. The Investigator must complete, sign and date the SAE pages, verifying the accuracy of the information recorded on the SAE pages with the corresponding source documents.

Additional follow-up information, if required or available, should all be faxed to CONRAD within one business day of receipt and this should be completed on a follow-up SAE form and placed with the original SAE information and kept with the appropriate section of the CRF and/or study file.

CONRAD will notify the U.S. Food and Drug Administration (FDA) and all participating investigators (i.e., all investigators to whom CONRAD is providing the relevant drug under its IND(s) or under any investigator's IND) in an IND safety report of potentially serious risks, from clinical trials or any other source, as soon as possible, but in no case later than 15 calendar days after CONRAD determines that the information qualifies for reporting under CFR 312.32(c)(1) which includes serious and unexpected suspected adverse reactions, findings from other studies, findings from animal or in-vitro testing, and increased rates of occurrences of serious suspected adverse reactions. In each IND safety report, CONRAD will identify all IND safety reports previously submitted to FDA concerning a similar suspected adverse reaction, and will analyze the significance of the suspected adverse reaction in light of previous, similar reports or any other relevant information.

CONRAD will notify the FDA of any unexpected fatal or life-threatening suspected adverse reactions as soon as possible, but in no case later than 7 calendar days after CONRAD initially receives the information.

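### Section 8.3.3 ties the later safety call for early leavers to a biopsy, while the adverse-event rules elsewhere run recording to a call with no such condition

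*Protocol*

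**What the plan says.** Protocol Section 8.3.3 applies to any woman who leaves after Visit 3 and before all genital sampling is done. It therefore covers women who stop after inserting the ring at Visit 4. It makes four statements:

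- Return visit: "the site may ask her to return for study procedures, if she is willing and if appropriate".
- AE question: "She will be asked about medications taken and AEs including genital symptoms since the last visit".
- Later call: "If she undergoes biopsy procedures, she will be contacted by telephone approximately one to two weeks after the biopsy".
- Exit: "She will be exited from the study during her last contact with the site".

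The recording rules are general. Section 13.1 has all AEs from Visit 3 recorded if they arise "by the time of the follow-up call one to two weeks after the last study visit". Section 13.1.3 sets the same limit for serious AEs (SAEs), "by the time of the follow-up call/contact one to two weeks after the last study visit", and Section 13.4 repeats it: "All SAEs whether or not considered a suspected drug reaction will be recorded starting with Visit 3", with the same end point. Section 9.10 describes the contact itself: "The site will contact the participant about one to two weeks after the completion of study visits". None of these mentions a biopsy. The opening of Section 9 plans one follow-up contact for each woman.

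Two other places bear on which rule a site will use. Section 13.3 points to 8.3.3 for the exit procedures of a woman discontinued for pregnancy. The visit instructions schedule the follow-up contact only at Visit 8, if that is her last visit (9.8), and at Visit 9 (9.9).

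**The concern.** Safety is the primary objective (6.2), and treatment-emergent AEs are the first primary endpoint (6.6.1). Section 14.6 counts them from ring insertion and gives no end date, so the end of the window is whatever the follow-up rules produce. Randomized women who do not complete sampling still contribute to the analysis (8.3.2).

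If a site treats 8.3.3 as the complete exit procedure, a ring user who leaves without a return biopsy is asked about the time since her last visit and then exited. A completer is asked again one to two weeks after her last visit. Late events would then be sought unequally, and the two sites could differ in what they do. Early leavers need not be a random subset: Section 14.8 itself counts early discontinuation for ring-related reasons. The analysis plan cannot repair this, because an event nobody asked about cannot be recovered afterwards.

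**Working it through.** The protocol states no figure to reproduce, so the check is a comparison of rules followed by day counts.

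**Step 1. The rules side by side**

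| Item | Section 8.3.3 | Sections 13.1, 13.1.3, 13.4, 9.10 |
|---|---|---|
| AE question at the discontinuation contact | Required, looking back to the last visit | Not addressed separately |
| Later contact | Stated only if there is a biopsy | Stated with no biopsy condition |
| Timed from | The biopsy | The last study visit (13.1, 13.1.3, 13.4) or completion of study visits (9.10) |
| Exit | At the last contact | After the follow-up contact (9.10) |

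Section 8.3.3 does not refer to 9.10, and neither 9.10 nor 13.1 says whether it covers discontinuers. A site can therefore read the general rule as applying, or treat the specific exit rule as complete. The visit instructions do not settle it, because a woman discontinued at Visit 5 or 6 never reaches Visit 8 or 9.

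**Step 2. A case the plan itself creates**

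Section 9.6 discontinues a woman with symptomatic bacterial vaginosis or trichomoniasis at Visit 6. No biopsy is scheduled at that visit.

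- Biopsy taken to mean one at the exit or return visit: no call is triggered. AE follow-up after her last visit can be 0 days, against the 7 to 14 days in 13.1.
- Visit 5 biopsy taken to count: Table 4 puts Visit 5 on ring Day 2 and Visit 6 on about Day 8. The call falls on Day 2 + 7 = 9 to Day 2 + 14 = 16. That is 9 − 8 = 1 to 16 − 8 = 8 days after Visit 6.
- Sensitivity to visit windows: insertion may be on cycle Day 6 to 8, so Visit 5 is on Day 7 to 9. Taking Visit 6 on Day 10 to 17, it follows Visit 5 by 10 − 9 = 1 to 17 − 7 = 10 days. The call then falls between 7 − 10 = −3 and 14 − 1 = 13 days after Visit 6. At one extreme it comes before she leaves.

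**Step 3. What a completer gets**

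Her last visit is 1 day (Visit 8) or 3 days (Visit 9) after ring removal, and the contact follows 7 to 14 days later. AE follow-up after removal is 1 + 7 = 8 to 3 + 14 = 17 days. For the Visit 6 leaver whose ring is removed at that visit, the first reading gives 0 days after removal. An unconditional contact gives 7 to 14.

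**Step 4. How many women**

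The protocol gives no early-exit rate. Assuming 5% to 15% of 50 to 60 randomized women, early exits number 0.05 × 50 = 2.5 to 0.15 × 60 = 9. At the 20% placebo share of 2:2:1 allocation, 0.5 to 1.8 of them would be on placebo. This bounds the extra calls. The number who lose follow-up is smaller if some have a return biopsy or the site applies 9.10.

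**The case against.** The strongest reply is that no conflict exists. Section 13.1 uses mandatory language for all AEs, 9.10 is not limited to completers, and Section 9 gives each woman a follow-up contact. Section 8.3.3 never waives that contact. It may only add a call after a biopsy, and the last contact at which she is exited can be the 9.10 call. Monitors also check that AEs and SAEs are properly documented (16.1). This reading is available, and it is why the point is an ambiguity. It does not remove the problem: 8.3.3 is the specific exit rule, 13.3 sends sites to it, and under this reading the biopsy condition would add little.

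It is also fair that the higher-risk leavers have rules of their own. These cover Grade 3 or 4 urogenital or product-related AEs (13.5.2), Grade 2 laboratory results (13.5.1), epithelial findings over 3 mm (Table 12), AE-driven unscheduled visits (9.11) and pregnancy after exposure (13.3). The gap mainly concerns women who leave for infection, personal reasons, exogenous hormones or non-adherence, or because an arm, site or the study stops.

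A reader might infer three stronger things that the protocol does not support:

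- That early leavers are not asked about AEs. Section 8.3.3 requires that question at the discontinuation contact.
- That a Visit 6 leaver has only a fifth to a third of a completer's AE window, counted from insertion. Much of that difference is shorter ring use and having no Visits 8 and 9. Only the missing 7 to 14 days come from 8.3.3.
- That a compulsory exit visit with colposcopy, safety bloods, lavage and swabs is needed. Safety bloods have no post-insertion draw before Visit 7 for any participant (12.2.3.1). Section 8.3.3 already allows appropriate procedures at a return visit, and off-window samples stay out of the time-point summaries (14.3). Leaving the return visit to the site and the woman's willingness is not itself a defect.

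**Conclusion.** The point holds as an ambiguity with a practical consequence. Under 8.3.3 as written, a site can end AE recording on the day a ring user without a return biopsy leaves, and so lose the 7 to 14 days of later follow-up that 13.1 expects. If the Visit 5 biopsy is allowed to trigger the call for a Visit 6 exit, the call comes 1 to 8 days after that visit on Table 4 timing.

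This rests on a site treating 8.3.3 as the complete exit rule, which the text permits but does not require. The number of women is probably small: about 3 to 9 early exits under the assumed 5% to 15%. The trial is descriptive and sized on feasibility, so no change in a conclusion can be shown, and the protocol does not establish that bias will occur. The change is worth making because it protects even ascertainment of the first primary endpoint and costs very little.

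**What to change.** In Section 8.3.3, replace the biopsy-conditional sentence, for women who have inserted a ring, with: *Every participant who discontinues after ring insertion, whether or not a biopsy is taken, will be contacted one to two weeks after ring removal or her last visit, whichever is later, to record AEs and medications (Section 9.10), and will then be exited.* Keep the existing post-biopsy call for women who leave before insertion, so that nobody loses a contact she now has.

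This brings 8.3.3 into line with 13.1, 13.1.3, 13.4 and 9.10. On Table 4 timing, a woman exited at Visit 6 with her ring removed that day would be contacted 7 to 14 days later, on ring Day 8 + 7 = 15 to 8 + 14 = 22. The cost is one sentence and one call per early exit, with no new procedure or visit.
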